## Abstract

**Introduction::**

Stable angina pectoris has a high prevalence and causes serious harm. Revascularization therapy can relieve angina pectoris to some extent, but it is not widely accepted in China due to the cost and secondary events. The Chinese proprietary medicine Danlou tablet has been widely used to treat angina pectoris, but previous trials had inadequate methodologies. In this study, we aim to conduct a randomized controlled trial to evaluate its efficacy and safety on stable angina.

**Methods and analysis::**

This study is a WeChat-based randomized, double-blind, and placebo-controlled clinical trial in China. Eligible participants are adults (aged 30–75 years) with CT-confirmed stable angina and traditional Chinese medicine-diagnosed intermingled phlegm and blood stasis syndrome. A total of 76 participants will be randomly allocated in a 1:1 ratio to the oral Danlou tablet group (1.5 mg a time, 3 times daily for 28 days) or the placebo group. Patients are permitted concomitant use of routine medications during these 28 days. The primary outcome is angina frequency per week. The secondary outcomes include angina severity, angina duration, traditional Chinese medicine efficacy, the withdrawal rate of emergency medications, blood lipids, and electrocardiograph efficacy. The WeChat app will be used to remind patients to take their medicines and fill out the forms. All data will be recorded in case report forms and analyzed by Statistical Analysis System software.

**Ethics and dissemination::**

This study has been approved by the Ethics Committee of Guang’anmen Hospital, China Academy of Chinese Medical Sciences in Beijing, China (No. 2019-225-KY).

**Trial registration number::**

ClinicalTrials.gov, ID: ChiCTR1900028068.

## Introduction

1

Coronary arterial disease (CAD) is the most common chronic noncommunicable disease, also the leading cause of death worldwide. The Global Burden of Disease Study 2017 reported that CAD had affected more than 110 million people and caused about 8.92 million deaths by 2016.^[1]^ Stable angina pectoris (SAP) is one of the main types of CAD. Angina is also the most painful symptom for the patients. In 2016, 9.4 million American adults and 11 million Chinese adults suffered from angina.^[2,3]^ Some surveys have shown that SAP associated with increased risks of cardiovascular endpoint events and all-cause mortality.^[4,5]^ That means we need to pay more attention to managing this disease. The guideline recommends lifestyle interventions, intensive medications, and reduction of risk factors as the basic treatments.^[6]^ Some patients still have persistent angina even after the basic treatments. Although percutaneous coronary intervention has proven to relieve angina and reduce the extent of myocardial ischemia,^[7]^ it is not widely accepted by patients in China. In 2017, an average of only 684 people per million cardiovascular patients had stent implantation.^[3]^ This could partly be due to the high cost and risk of revascularization: people may face a 5% to 10% risk of restenosis within 1 to 5 years^[8,9]^ and still have substantial mortality and morbidity rates.^[10,11]^ These problems suggest that there is an unmet need to develop new therapies for SAP.

In China, a proprietary medicine named Danlou tablet (DLT), has long been considered as a common therapy for SAP. DLT is composed of 10 kinds of Chinese herbal medicines (see Table 1), and the indication for it is treating coronary artery disease with “intermingled phlegm and blood stasis” syndrome. Clinical studies have shown DLT could reduce the frequency and duration of angina pectoris, and improve cardiac function. In recent years, several studies on DLT have been carried out.^[12,13]^ Animal experiments have shown that DLT is efficient in strengthening the protection of vascular endothelium, reducing the levels of inflammatory mediators, and stabilizing atherosclerotic plaques.^[14,15]^ A metabolomics study has revealed that the mechanisms underlying the effects of DLT in the treatment of CAD involve the inhibition of epidermal growth factor receptor expression and the activation of the mitogen-activated protein kinase signaling pathway by regulating glycerophospholipid metabolism and energy metabolism.^[16]^

**Table 1 T1:** Components of Danlou tablet.

Chinese name	English name	Origin	Pharmacological effects
Gua Lou Pi	*Trichosantheskirilowii*	The dried peel of *Trichosantheskirilowii Maxim*	Antiatherosclerotic, and vascular endothelium protection^[17]^
Xie Bai	*Allium macrostemon*	The dried bulb of *Allium macrostemon*	Antiatherosclerotic, antioxidant, antihyperlipidemic, and anticoagulation^[18]^
Ge Gen	*Pueraria montana var. lobata*	The dried root of *Pueraria montana var. lobata*	Antihypertensive, cardiac protection, and antiatherosclerotic^[19]^
ChuanXiong	*Conioselinumanthriscoides* “*Chuanxiong*”	The dried rhizome of *Conioselinumanthriscoides* “*Chuanxiong*”	Antiplatelet aggregation, antithrombotic and anti-inflammatory^[20]^
Dan Shen	*Salvia miltiorrhiza*	The dried root or rhizome of *Salvia miltiorrhiza*	Antiplatelet aggregation, myocardium protection and antiatherosclerotic^[21]^
Chi Shao	*Paeonia anomala subsp. veitchii*	The dried root of *Paeonia lactiflora*	Promoting angiogenesis, analgesia and anti-inflammatory^[20]^
Ze Xie	*Alisma plantago-aquatica subsp. orientale*	The dried tuber of *Alisma plantago-aquatica subsp. orientale*	Antiatherosclerotic, antihypertensive, and anti-inflammatory^[22]^
Huang Qi	*Astragalus mongholicus*	The dried root of *Astragalus mongholicus*	Myocardium protection, promotion of microcirculatory and anti-inflammatory^[23]^
Gu Sui Bu	*Drynariaroosii*	The dried rhizome of *Drynariaroosii*	Promoting angiogenesis and anti-inflammatory^[24]^
Yu Jin	*Curcuma aromatica*	The dried root tuber of *Curcuma aromatica*	Analgesia, promoting blood circulation and lower blood viscosity^[25]^

Although several studies have reported the effective role of DLT in the treatment of stable angina, the evidence is not sufficiently strong to support clinical decision making for the low quality of methodology. WeChat is an instant messaging app used by practically everyone in China, capable of transmitting various texts, voices, pictures, and video material. Using WeChat, we will conduct an objective superiority trial to investigate the efficacy and safety of DLT in patients with SAP.

## Methods

2

### Study design

2.1

Through a randomized, double-blind, and placebo-controlled clinical trial, we will investigate the curative efficacy and safety of DLT in patients with SAP. The trial will include a 1-week screening period and a 4-week treatment period. We plan to enroll 76 participants, who will be allocated randomly in a 1:1 ratio by a central randomization system (CRS) into the intervention group and the control group. Following the original medication regimen, participants will take DLT or placebo 3 times per day. This trial has already been registered at the Chinese Clinical Trial Registry on December 9, 2019 (ChiCTR-1900028068), following the principles of the Declaration of Helsinki and Good Clinical Practice guidelines. We will strictly follow the Consolidated Standards of Reporting Trials (CONSORT 2017)^[26]^ and the Standard Protocol Items: Recommendations for Interventional Trials (SPIRIT 2013)^[27]^ for the research design. A flow diagram illustrating our study design is presented in Figure 1.

**Figure 1 F1:**
[figure not shown]
flow diagram for DLT study design. DLT = Danlou tablet.

### Participant recruitment

2.2

In the present study, 76 participants will be recruited between September 2020 and December 2021 in Guang’anmen Hospital, China Academy of Chinese Medical Science, Beijing. The main forms of recruitment will be advertisements posted on WeChat, webpages, and notice boards. The advertisements will focus on a brief description of what this study aims for and how to participate. In addition, cardiologists in the hospital will identify outpatients with SAP and suggest them to participate in the study. After 2 researchers both confirm that a participant meets the inclusion and exclusion criteria, he or she can sign the informed consent form and join the trial.

### Inclusion criteria

2.3

The inclusion criteria are the following:

(1)patients diagnosed with SAP with “intermingled phlegm and blood stasis syndrome;”(2)age ranging from 30 to 75 years;(3)voluntary participation;(4)using WeChat.

In respect of the diagnosis of SAP, we refer to the 2019 European Society of Cardiology Guidelines for the Diagnosis and Management of Chronic Coronary Syndromes,^[6]^ the Society for Cardiovascular Angiography and Interventions/American College of Cardiology/American Heart Association Expert Consensus Document: 2014 Update on Percutaneous Coronary Intervention Without On-Site Surgical Backup.^[28]^ Participants with a pre-test probability of >15% are recommended to undergo a coronary dual-source CT angiography. Based on the CT angiography results, patients are diagnosed with SAP in the case of at least 1 major coronary branch stenosis of more than 50%. Participants should also have typical SAP symptoms.

In respect of the diagnosis of “intermingled phlegm and blood stasis syndrome,” we refer to the Diagnostic Criteria for Syndrome Elements of Coronary Heart Disease Angina published by the Chinese Society of Traditional Chinese Medicine Cardiovascular Disease Branch in 2018.^[29]^ Syndrome elements are the smallest diagnostic units for the diagnosis of traditional Chinese medicine (TCM) syndromes. A diagnosis of “phlegm syndrome” and “blood stasis syndrome” is made if the summed scores of single syndrome elements ≥8 points. When the criteria of both syndromes are met, the “intermingled phlegm and blood stasis syndrome” is diagnosed.

### Exclusion criteria

2.4

Participants meeting any of the following criteria will be excluded from the trial.

(1)Patients who have previously experienced unstable angina pectoris and/or acute myocardial infarction; other diseases that may cause chest pain, such as congenital heart diseases, valvular diseases, and severe neurosis; arrhythmia; heart function of grade III or IV.(2)Acute stage of cerebral infarction.(3)Patients with severe liver- and/or kidney-related diseases; patients whose alanine aminotransferase and aspartate aminotransferase levels are higher than 1.5 times the upper limit of the normal range; patients with abnormal renal function.(4)Acute infection within the last 2 weeks.(5)Patients with other serious diseases that require treatment (like tumors, hematonosis, diabetes complications, etc).(6)Mental disorders or mental retardation which prevent the participant from completing the questionnaire.(7)Pregnant and lactating women.(8)Tendency to bleed; abnormal disseminated intravascular coagulation or international normalized ratio; low platelet levels.(9)Participation in other clinical trials within the last month.(10)Allergic constitution or allergy to the constituents of the drugs.(11)Unable to read or listen to the materials sent via WeChat (words, audio, and images).

### Removal and discontinue criteria

2.5

A participant will be removed under the following circumstances:

(1)violations of the inclusion and/or exclusion criteria;(2)refusal to undergo required examinations;(3)failure to take drugs during the treatment period;(4)myocardial infarction or sudden cardiac events.

A participant has the right to drop out at any time during the treatment; however, his or her reasons for withdrawal must be recorded in the case report form (CRF). According to the intention-to-treat principle, their last data will be involved in the final analysis. Under the following circumstances, the trial might be discontinued:

(1)participants begin to have serious adverse reactions after taking DLT;(2)participants begin to show high sensitivity to the medication, such as headache, stomach ache, diarrhea, and other discomforts;(3)masking and randomization fail.

### Randomized design, blinding, and allocation concealment

2.6

In order to reduce selection bias and balance various non-research factors among groups, we will adopt a randomized block design and allocation concealment. The participants will be randomized in a 1:1 ratio into the DLT group and the placebo group, in 4 blocks of 19 participants. Random numbers from 1 to 76, as well as group numbers, will be generated by Statistical Analysis System software in CRS managed by the Clinical Evaluation Center of the China Academy of Chinese Medical Science. After inputting a participant's information into CRS, a random number will be generated. After the participant signs informed consent, the researcher obtains the corresponding group number from CRS. Neither of the participants and researchers will be allowed to know the random numbers and group numbers. In order to keep the study double-blind, DLT and the placebo will have the same appearance, smell, taste, and weight. The allocation will not be revealed until the end of the study, unless serious adverse events (AEs) happen. If an individual begins to show serious adverse reactions, the case will be reported to the Ethics Committee, and the blinding will be uncovered by the principal researcher. Then the participant will be removed from the study, and the related data will be recorded. If the emergency events exceed 20% of the sample content, the clinical trial will be discontinued, and the results will be deemed invalid.

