### Statistical analysis

2.16

Statistical analyses consist of 3 parts—baseline comparability analysis, efficacy analysis, and security analysis. An independent statistician will be in charge of the analyses, and Statistical Analysis System (version 9.2) will be used. All tests are 2-sided, and *P* < .05 is considered to indicate statistical significance. According to the intention-to-treat principle,^[32]^ there will be 3 analysis sets: the full analysis set, the per-protocol analysis set, and the safety analysis set. Participants who insist in taking medication for 2 weeks will be involved in the full analysis set group; if a critical variable is missing in any given case, the statistician will consider the last observation result as the final data. Patients who conform to the treatment plan will be included in the per-protocol analysis set group. The Mantel–Haenszel Chi-squared test and analysis of covariance will be conducted in the case of important baseline non-comparability. Normally distributed quantitative data will be presented as mean ± standard deviation and analyzed by Student *t* test. Non-normally distributed quantitative data will be presented as median and interquartile range and analyzed by the Kruskal–Wallis test. Ordinal data, like ECG efficacy, will be analyzed by the Kruskal–Wallis test. Qualitative data will be presented as percentage and rate and analyzed by the Chi-square test and Fisher exact test. The paired Student *t* test will be used to analyze significant differences between pre- and post-treatment. Moreover, subgroup analysis will be conducted according to gender, age, and complications to explore the internal consistency of the conclusions. For the safety analysis, the statistician will adopt the safety analysis set to evaluate the incidence rate of AEs and the change of laboratory indices. Both AEs and laboratory indices are described in lists and analyzed by the chi-square test or Student *t* test.

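### Section 2.6 credits unstratified blocks with balancing patient factors, and the default primary test in section 2.16 uses neither block nor baseline attack frequency

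*Protocol article*

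**What the plan says.** Section 2.6 gives the purpose of the design: "to reduce selection bias and balance various non-research factors among groups, we will adopt a randomized block design and allocation concealment". The scheme follows: "The participants will be randomized in a 1:1 ratio into the DLT group and the placebo group, in 4 blocks of 19 participants". The section does not say how blocks are formed and names no factor that defines them. Numbers run from 1 to 76, and "After inputting a participant's information into CRS, a random number will be generated". Section 2.2 sets a single site and the window: "76 participants will be recruited between September 2020 and December 2021 in Guang’anmen Hospital".

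Section 2.8.1 defines the primary outcome as the change in attack frequency from baseline to week 4, and Table 3 schedules attack frequency on the inclusion day, so the baseline value is collected.

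Section 2.16 fixes the between-group tests: "Normally distributed quantitative data will be presented as mean ± standard deviation and analyzed by Student *t* test". Quantitative outcomes that fail normality go to the Kruskal–Wallis test instead. Neither test carries a term for block or for baseline. Analysis of covariance and the Mantel–Haenszel test appear there only as a response to important lack of comparability at baseline.

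**The concern.** Two things do not fit together. First, the reason given for blocking is a property that blocking without stratification does not add. A reader of 2.6 would expect some protection for patient factors beyond that of simple randomization, and nothing in the scheme supplies it. Second, what the blocks do control is not used in the analysis, and the factor most likely to predict the outcome, baseline attack frequency, enters only if a difference is noticed after the data are in.

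At stake is a little precision, and whether adjustment is fixed in advance or triggered by what is observed. The validity of the comparison is not at stake.

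**Working it through.** **The plan's own figures.** From section 2.11: means 1.90 and 2.55 per week, SDs 0.45 and 1.03, difference 0.65, two-sided 5%, power 90%.
- Common SD: sqrt((0.45² + 1.03²)/2) = 0.795.
- Per group, normal approximation: (0.45² + 1.03²) × (1.960 + 1.282)² / 0.65² = 31.4, so 32. The stated 27 matches a one-sided 5% test (t-based power 0.904 at 27). That is a separate matter, noted only because the same inputs are used below.
- 30/(1 − 0.20) = 37.5, so 38 per group and 76 in total. This step reproduces.

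**What the blocks do for a patient factor.** For a baseline factor unrelated to entry order, the standardized difference between arms of 38 has standard error sqrt(2/38) = 0.229. The chance that it exceeds 0.3 SD is 2 × (1 − Φ(0.3/0.229)) = 0.191. Simulated lists with four blocks of 19 gave an average of 0.191 over six sets of 8,000 lists (range 0.180 to 0.196). The blocks leave the figure where simple randomization puts it. For four independent factors, the chance that at least one exceeds 0.3 SD is 1 − (1 − 0.191)⁴ = 0.572. The 0.3 threshold and the four factors are illustrative.

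**What leaving block out costs.** The documents give no between-block variance. Let ρ be the share of outcome variance that lies between blocks, assumed to be 0 to 0.10, with total SD held at 0.795. Each simulated trial has four permuted blocks, each odd block splitting 9:10 or 10:9 at random. The t test and a linear model with a block term are applied to the same data. With all 76 analysed (6,000 null runs; 3,000 runs at a difference of 0.65):

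| ρ | SE, t test | SE, with block | Excess | Type I, t test | Type I, with block | Power, t test | Power, with block |
|---|---|---|---|---|---|---|---|
| 0 | 0.181 | 0.182 | none | 0.049 | 0.049 | 0.938 | 0.936 |
| 0.05 | 0.181 | 0.178 | about 2% | 0.044 | 0.050 | 0.946 | 0.949 |
| 0.10 | 0.180 | 0.173 | about 4% | 0.041 | 0.050 | 0.950 | 0.959 |

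With 30 per arm analysed, power without and with block is 0.873 and 0.872 at ρ = 0, 0.884 and 0.890 at 0.05, and 0.895 and 0.910 at 0.10. The loss is therefore 0 to 1.5 points.

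The actual spread of the estimate does not grow with ρ: its standard deviation is 0.181 at ρ = 0 and 0.172 at 0.10. Only the reported standard error is too wide.

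**Degrees of freedom.** The t test has 76 − 2 = 74. Block takes 3 and baseline frequency 1, leaving 70.

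The gain from adjusting for baseline frequency depends on its correlation with the week 4 value, which the documents do not give, so it is not quantified here.

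**The case against.** The case against is strong on several points.

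- The sentence in 2.6 credits blocking and concealment within a randomized design. Randomization balances known and unknown factors in expectation, and leaving block out of a test does not undo balance made by the design. This stands. A reader might infer that the claimed balance is absent; the documents do not support that. Only the extra balance attributed to the blocks is missing.
- A reader might also infer that the standard error is inflated as a matter of fact. It is not known to be. The excess needs outcome differences between blocks, for which the documents give no figure, and it makes the test conservative. This stands.
- That blocks follow recruitment order is inferred from numbers being issued as participants are entered. Four months per block (16/4) would further assume even accrual. The mention of cold and wind in 2.8.1 is one descriptor on the angina severity scale, not a statement that attack frequency varies by season. A change-from-baseline outcome also removes stable differences in level between periods. All of this stands and points to the lower end of the assumed range.
- The 19% and 57% figures describe any unstratified trial of this size. This stands; they show that the blocks do not help, not that the trial is unusually exposed.
- Unadjusted analysis after unstratified blocks is common, model terms are often left to an analysis plan, and 2.16 does provide analysis of covariance. This stands only in part. Section 2.16 does fix a default test and makes adjustment depend on observed imbalance, and that choice can be improved now.

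**Conclusion.** The point holds as a minor one. Section 2.6 claims for the blocks a balance on patient factors that they do not add, and the default tests in 2.16 use neither the blocks nor a baseline value already collected. If 0 to 10% of outcome variance lies between blocks, the reported standard error is about 0 to 4% too wide and power is lower by roughly 0 to 1.5 points, with no bias and no excess type I error. These sizes rest on the section 2.11 SDs, the assumed variance share, and blocks that run along the list. Nothing here threatens the validity of the comparison.

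Even balance of numbers is only approximate: a block of 19 cannot split 1:1, so each is at best 10:9. If the odd place is assigned at random, the arms differ by about 1.5 on average and by as much as 40 to 36. That is a separate defect in the same sentence.

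**What to change.** In 2.16, pre-specify the primary comparison as a linear model (analysis of covariance) for the change in attack frequency, with treatment, randomization block and baseline attack frequency, fitted whether or not imbalance is observed. The planned t or Kruskal–Wallis test can stay as a sensitivity analysis. In 2.6, limit the stated purpose of blocking to keeping group numbers close along the list.

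The cost is about 4 degrees of freedom and two text changes. If blocks do not differ, the block term costs next to nothing (power 0.938 without and 0.936 with it at ρ = 0).

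Stratifying the list by baseline frequency is optional and is more than a system setting. Blocks of 19 within two strata of a 76-person trial would probably end incomplete and would replace the four trial-wide blocks, so the block scheme would have to be redesigned.

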Validation	The decrease of ST segment is to increase by more than 0.05 mV after treatment, but it does not reach the normal level. In the main electrocardiographic lead, the T wave changes lighter (up to 25%); or the T wave changes from flat to upright, improvement of atrioventricular or ventricular block.
Invalidation	The ECG is basically the same as before treatment.
Aggravation	The ST segment is to decrease by more than 0.05 mV after treatment. In the main electrocardiographic lead, the T wave changes deeper (up to 25%); or the T wave changes from upright to flat, or the upright T wave becomes inverted, and an ectopic rhythm, atrioventricular or ventricular block.

**Table 3 T3:** Schedule of data collection.

	Screening stage		Inclusion day	Treatment period	
Items	-7th Day	-1th Day	0th Day	2th Week	4th Week
Informed consent	√				
Inclusion/exclusion criteria			√		
Demographic data	√				
General clinical data	√				
Anginal frequency			√	√	√
Anginal severity and duration			√	√	√
TCM effect			√	√	√
Electrocardiograph			√		√
Blood Lipid		√			√
Vital signs		√			√
Blood pressure		√			√
Blood and urine routine		√			√
Stool routine and occult blood		√			√
Liver and renal function		√			√
Record adverse events				√	√

Checked boxes indicate the indices tested during a specific time period. General clinical data include medical history, course of the disease, treatment history, concomitant diseases, and concomitant medications. Vital signs include body temperature, respiration rate, heart rate, and blood pressure. CRF = case report form, TCM = traditional Chinese medicine.

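### Section 2.6 specifies 1:1 allocation in blocks of 19, but an odd block cannot be split 1:1, so the scheme contradicts itself and does not guarantee the implied 38:38 split

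*Protocol article*

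**What the plan says.** **Block scheme.** Section 2.6 gives the ratio and the block size in one sentence: "The participants will be randomized in a 1:1 ratio into the DLT group and the placebo group, in 4 blocks of 19 participants". Section 2.1 repeats the 1:1 ratio for a total of 76. The list has the same length: "Random numbers from 1 to 76, as well as group numbers, will be generated by Statistical Analysis System software in CRS". No within-block split is given, and 38 per arm is not printed; it follows from 76 at 1:1.

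**Order of steps.** Three places describe how a participant reaches allocation.

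- Section 2.2: two researchers confirm the criteria, and then "he or she can sign the informed consent form and join the trial".
- Section 2.6: on entry of the participant's "information into CRS, a random number will be generated". The next step is: "After the participant signs informed consent, the researcher obtains the corresponding group number from CRS". Eligibility is not mentioned at either step.
- Table 3 (in Section 2.8.1): consent is ticked at day -7, the blood, liver and renal tests at day -1, and the row "Inclusion/exclusion criteria" only at day 0.

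**The concern.** Blocking exists to return the arms to the intended ratio at the end of every block. A block of 19 cannot do that at 1:1. A programmer building the list from this text would have to guess what was meant: blocks of 19 that lean one way or the other, in some unstated pattern, or a different block size altogether. These are different schemes, with different balance over the recruitment period and different predictability.

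The Discussion faults earlier studies of this product for their randomisation, allocation concealment and blinding, and Section 2.5 lists failed masking and randomisation among the reasons for discontinuing. The randomisation rule should therefore be one that can be carried out as printed.

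The secondary issue is the order of steps. If the three descriptions disagree, it is unclear whether a number or group can be assigned to someone who has not consented or whose eligibility tests are not yet available.

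**Working it through.** **1. Reproduce the total.** Inputs from Section 2.11: 30 per group, 20% dropout. 30 / (1 − 0.20) = 37.5, rounded up to 38 per arm; 2 × 38 = 76. From Section 2.6: 4 × 19 = 76. The totals agree.

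**2. Check the block against the ratio.** 19 / 2 = 9.5, so the nearest possible splits are 9:10 and 10:9. No block can be 1:1.

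**3. What overall split can result?** Assume each block is 9:10 or 10:9, independently and with equal probability. Let k be the number of the four blocks with 10 on Danlou. The Danlou total is 36 + k, with k binomial (4, 0.5).

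| Danlou : placebo | Ways out of 16 |
|---|---|
| 36:40 | 1 |
| 37:39 | 4 |
| 38:38 | 6 |
| 39:37 | 4 |
| 40:36 | 1 |

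So P(38:38) = 6/16 = 37.5%; P(37:39 either way) = 8/16 = 50%; P(36:40 either way) = 2/16 = 12.5%.

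If instead two blocks are fixed at 10:9 and two at 9:10, the Danlou total is 2 × 10 + 2 × 9 = 38 with certainty. The text does not say which applies.

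**4. Effect on power.** Inputs from Section 2.11: SD 0.45 (treatment), SD 1.03 (reference), difference 0.65, two-sided alpha 0.05. All 76 are taken as analysed.

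SE = √(0.45²/n_T + 1.03²/n_C); power = Φ(0.65/SE − 1.96).

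- 38:38: SE = √(0.2025/38 + 1.0609/38) = 0.1823; power 94.6%.
- 36 Danlou, 40 placebo: SE = √(0.2025/36 + 1.0609/40) = 0.1793; power 95.2%.
- 40 Danlou, 36 placebo: SE = √(0.2025/40 + 1.0609/36) = 0.1858; power 93.8%.

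The largest loss is 0.8 percentage points.

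**5. Block sizes that would work.** The even divisors of 76 are 2, 4, 38 and 76. Nineteen blocks of 4, each 2:2, give 19 × 4 = 76 and exactly 38:38. The printed figures may be this scheme with the two numbers transposed; that is an assumption. Mixed sizes also fit: 10 × 4 + 6 × 6 = 76.

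**6. Set the sequences side by side.**

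| Source | Order |
|---|---|
| Section 2.2 | eligibility, then consent |
| Section 2.6 | data entry and random number, then consent, then group number |
| Table 3 | consent (day -7), laboratory tests (day -1), eligibility (day 0) |

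Section 2.2 and Table 3 cannot both be followed. The exclusion criteria in Section 2.4 include liver enzymes, renal function and platelets, while Table 3 places the blood, liver and renal tests six days after consent. On that schedule eligibility cannot be fully confirmed before consent. Section 2.6 makes release of the group number depend on consent alone; read with Table 3, that would permit allocation before eligibility is established.

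**The case against.** Several points against a stronger reading are sound.

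- A reader might infer that the list cannot produce 38:38. That does not follow. Four odd blocks can sum to 38:38, and will do so with certainty if two lean each way. The supportable statement is that balance is not guaranteed as printed.
- The 37.5% figure depends on independent, equally likely 9:10 and 10:9 blocks, which the article does not state.
- A reader might infer that the sample size is undermined. It is not: even 36:40 leaves power at 93.8% or above on the plan's own inputs. Near-equal blocks of 19 also still restrain imbalance; 76 unrestricted coin tosses would give 38:38 with probability only C(76,38)/2^76 = 9.1%.
- A reader might infer that anyone entered who then declines uses up one of the 76 numbers, and that such losses could be steered by the researcher. The article does not say whether an unused number is lost or reissued, and a condensed article may leave that to the randomisation procedure. The group number is released only after consent, so the described route reveals no allocation at the time of a refusal. Drawing a number before consent does not in itself prevent balance.
- The remedy may be no more than a wording correction, if 19 blocks of 4 was meant.

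What remains is the parity error and the conflicting sequences. Neither is a detail left to a fuller document: the article prints a block size that is incompatible with the ratio in the same sentence, and it prints orders of consent and eligibility that disagree.

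**Conclusion.** The block rule is wrong as printed: 1:1 allocation and blocks of 19 are incompatible, and the 38:38 split implied by 76 participants at 1:1 is not assured. Under the independence assumption the exact split occurs with probability 37.5%, and with near-equal blocks the worst case is 36:40. The cost in power is negligible, so the point rests on an internally inconsistent randomisation specification, not on lost precision. The parity error is certain; the probabilities are conditional on the assumed within-block splits.

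The conflict between Section 2.2, Section 2.6 and Table 3 is real but secondary. The documents do not show that list positions are lost or that concealment is broken by this route. Overall this is a moderate correction, not one on which the validity of the trial turns.

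**What to change.** **Block scheme.** Replace the block statement in Section 2.6 with permuted blocks of even size that sum to 76. Nineteen blocks of 4 would do; so would a mix such as ten blocks of 4 and six of 6. Keep the sizes in a randomisation document withheld from site staff, and let the protocol say only that blocks are permuted, of even size and undisclosed. Since 4 and 19 are already in print, mixed sizes are the safer choice. If the list has already been used, report the scheme actually applied instead of regenerating it.

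**Sequence.** Align Section 2.2, Section 2.6 and Table 3 so that a number is assigned only after both consent and day-0 confirmation of eligibility.

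**Cost.** Regenerating a list of 76 in the central system, and editing two paragraphs to agree with Table 3. The small downside is that short blocks are somewhat easier to guess at a single site; mixed, undisclosed sizes largely offset this.
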